SOAR partner Elizabeth Glaser Pediatric AIDS Foundation (EGPAF) proposes to leverage existing and planned service delivery platforms in Swaziland to evaluate a model of care to improve pediatric retention and ART adherence. In the family-centered care (FAM-CARE) program, after identification of HIV infection in a child, active HIV testing of all family members is conducted and all HIV-positive family members are seen together as a unit and receive their care together. EGPAF-Swaziland is in the process of establishing a FAM-CARE service delivery program in selected health facilities in the Hhohho region of Swaziland, and roll-out of these services will provide a platform for this study. Viral load monitoring is in process of national roll-out in Swaziland. The planned study is an implementation science study to evaluate the implementation of the FAM-CARE program in Swaziland and its effect on viral suppression and retention in children living with HIV.

The proposed study will evaluate the effect of implementing a FAM-CARE program on viral suppression and retention in children through enrollment of a prospective cohort of HIV-positive children and their caregivers at sites implementing the FAM-CARE program and control sites continuing the current standard of care. The study will be conducted in four “clusters” of facilities (2 hospitals and 2 health centers and their filter clinics) in the Hhohho region of Swaziland. Two facility “clusters” (one hospital and one health center, with their filter clinics) will be randomized to initiate the FAM-CARE program with viral load monitoring and two “clusters” (one hospital and one health center, with their filter clinics) will be control standard-of care sites. A prospective cohort of HIV-positive children and their caregivers will be followed in the FAM-CARE program sites and control sites. Each child will be followed for 18 months following enrollment. The primary objective is to evaluate the effect of the FAM-CARE program on the rates of viral suppression and retention in care, comparing rates of viral suppression and retention in children enrolled in FAM-CARE vs control sites. The study will also evaluate factors associated with viral suppression and retention (including family demographic characteristics), and conduct qualitative interviews to assess the acceptability of the FAM-CARE program by caregivers and health care providers in the intervention sites.

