The primary study endpoints are the proportion of children on ART with viral suppression (defined as HIV RNA below the level of assay detection) and the proportion with HIV RNA >1,000 copies/mL at 18 months. The tables below show the minimum number of children receiving ART needed to demonstrate significant (0.05) effects of the FAM-CARE program on viral suppression and HIV RNA >1,000 copies/mL compared to control facility care, assuming different viral suppression and HIV RNA >1,000 copies/mL rates in the control group.

**Table 3** (viral suppression) shows the minimum sample size per arm and overall needed to demonstrate a significant FAM-CARE program effect with 80% power at 5% significance levels, assuming different levels of viral suppression in children on ART from control facilities (ranging between 65-85% suppression) and different levels of improvement that could be observed in children in FAM-CARE program sites compared to control sites. With 398 HIV-positive children receiving ART from unique families, we will have 80% power to detect at least a 10% increase in viral suppression with FAM-CARE, assuming a viral suppression rate between 65% and 80% in control children on ART.

**Table 3.** Sample size estimates for detecting FAM-CARE effects on viral suppression rates

| % Viral Suppression in Control | Minimum Effect of FAM-CARE | % Viral Suppression in FAM-CARE Sites | Alpha | Power | Sample size/ arm | Total sample size | Adjusted for 10% LTFU |
| --- | --- | --- | --- | --- | --- | --- | --- |
| .65 | .15 | .80 | .05 | 80% | 138 | 276 | 308 |
| .65 | .20 | .85 | .05 | 80% | 73 | 146 | 164 |
| .65 | .25 | .90 | .05 | 80% | 43 | 86 | 96 |
| .70 | .15 | .85 | .05 | 80% | 121 | 242 | 270 |
| .70 | .20 | .90 | .05 | 80% | 62 | 124 | 138 |
| .75 | .15 | .90 | .05 | 80% | 100 | 200 | 224 |
| .80 | .10 | .90 | .05 | 80% | 199 | 398 | 444 |
| .85 | .05 | .90 | .05 | 80% | 686 | 1372 | 1526 |

**Table 4** (HIV RNA >1,000 copies/mL) shows the minimum number of children required to detect at least a 5%, 10%, or 15% improvement with FAM-CARE care sites compared to control sites, with 80% power at 0.05 significance level, assuming different HIV RNA >1,000 copies/mL rates in control children (ranging from 10-30%).

**Table 4:** Sample size estimates for detecting FAM-CARE effects on HIV RNA >1,000 c/mL

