Caregiver-child pair information will be collected through caregiver interviews and review of facility, laboratory and patient records. Study nurses will be trained to interview caregivers and abstract data from the facility records using electronic data capture forms. Participant-specific data collection forms will be identified with the participant’s unique study identification number. Participant names will not be included in the study database. All electronic tablets will be password protected, with access to only key study personnel.

*3. Statistical Analysis Plan*

First, we will summarize baseline characteristics of participants using means (standard deviations) or medians (IQR) for continuous variables and proportions for categorical variables, stratified by FAM-CARE/control arms. We will identify characteristics that differ significantly between the two study arms. Since participation in the FAM-CARE program is voluntary, we will assess for potential selection bias in the FAM-CARE sites by comparing characteristics of families that decline to families that accept FAM-CARE.

The primary objective of this study is to evaluate the effect of a FAM-CARE program of HIV care on the proportion of HIV-positive children on ART with viral suppression (defined as viral load below the level of assay detection) and the proportion of HIV-positive children on ART with HIV RNA >1000 copies/mL 18 months after enrollment. We will estimate the respective proportions and associated confidence intervals by study arm. Below we outline potential approaches to estimating the effect of FAM-CARE depending on comparability of the study arms:

a) If the FAM-CARE program decline rate is low (say, <10%) and baseline characteristics of children in FAM-CARE and control sites are fairly similar, we will estimate the proportion of HIV-positive children on ART with viral suppression and associated confidence intervals by study arm. Using a simple chi-square test, we will compare the two proportions at 5% significance level. The proposed chi-square test assumes outcomes from enrolled children are independent.

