However, there is potential correlation of viral outcomes of children from the same family as well as children from the same facility, thereby violating the assumption of independence required for validity of the chi-square test. We propose to use multilevel generalized linear models to account for the potential intra-cluster correlation due to family unit and facility. In addition, we will adjust for potential confounding that may arise due to imbalances in children’s characteristics between study arms.

b) If the FAM-CARE program decline rate is substantial (>10%) and baseline characteristics of children differ significantly between those who accept FAM-CARE and those who decline, we propose to use the propensity score method to match and compare FAM-CARE and non- FAM-CARE participants. Using data from the FAM-CARE sites, we will estimate the probability of accepting FAM-CARE program given the baseline children and family characteristics. Using special matching algorithms, we will develop a statistical control group that will be compared with the FAM-CARE group. Regression modeling will be used to estimate the effect of the FAM-CARE group compared to the control group.

c) Finally, we will perform an intent-to-treat analysis in which all children at facilities offering the FAM-CARE program will be compared to all children at facilities without FAM-CARE program.

To answer primary aim 2, we will use the same statistical approach described for specific aim 1 above.

To answer secondary objectives 1 and 3, the analysis for the primary objective described above will be repeated using the appropriate outcomes.

To identify factors associated with viral suppression and HIV RNA >1,000 copies/mL (secondary objective 2), we propose to use multilevel logistic regression models to estimate the association between viral suppression and putative factors in each study arm. Examples of factors that might be evaluated include age and gender of child, when ART initiated and ART regimen, serious illness or hospitalization, timeliness of pharmacy drug pick-up, school attendance, family size, number of other HIV-positive individuals in family, HIV treatment and clinical status of other HIV-positive family members, disclosure of HIV status within family.

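### Two primary endpoints each take the full 5% with no order or joint rule, so if success on either counts, the chance of a false primary claim can exceed 5%

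*Protocol*

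**What the plan says.** The Research Goals and Objectives section lists two primary objectives, each with its own hypothesis: suppression at 18 months, and HIV RNA >1,000 copies/mL at 18 months. Sample size estimation repeats this: "The primary study endpoints are the proportion of children on ART with viral suppression" "and the proportion with HIV RNA >1,000 copies/mL at 18 months".

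The Statistical Analysis Plan (under Data Collection and Management) says of suppression: "Using a simple chi-square test, we will compare the two proportions at 5% significance level". It then notes that outcomes may be correlated within family and facility, and proposes multilevel models. For the second endpoint it says: "To answer primary aim 2, we will use the same statistical approach described for specific aim 1 above".

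Table 3 gives the numbers "needed to demonstrate a significant FAM-CARE program effect with 80% power at 5% significance levels" for suppression. Table 4 does the same for RNA >1,000, again with alpha 0.05 and 80% power.

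Other sections describe the primary set differently. The Summary of Proposed Research says "The primary objective is to evaluate the effect of the FAM-CARE program on the rates of viral suppression and retention in care" and does not mention RNA >1,000 in that objective. The objectives section places loss to follow-up among the secondary objectives. Expected Results refers to viral suppression as the (single) primary endpoint.

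**The concern.** Two primary hypotheses, each with a full 5% test, give two chances of a positive primary result. Unless the plan says which test comes first, divides the alpha, or requires both to succeed, a reader may take a significant result on either one as showing that the program works. That conclusion then carries more than the 5% error attached to each comparison. It matters because the Summary says that an effective program will be taken to the Ministry of Health for wider roll-out. The differing descriptions of the primary set make it harder to tell afterwards which result was meant to decide the question.

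**Working it through.** **Step 1: the plan's own sample size.** Inputs from Tables 3 and 4: 80% vs 90% suppressed (equivalently 20% vs 10% above 1,000), alpha 0.05, power 80%, loss 10%. Two-sided test, pooled variance, no continuity correction:

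n = [1.96 × √(2 × 0.85 × 0.15) + 0.8416 × √(0.8 × 0.2 + 0.9 × 0.1)]² / 0.10² = (0.990 + 0.421)² / 0.01 ≈ 199 per arm.

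199 / 0.9 rounds up to 222 per arm, or 444 in total, as stated. All 18 per-arm values in the two tables reproduce in the same way. So each endpoint is planned at the full two-sided 0.05, and no alpha is set aside for a second primary test.

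**Step 2: correlation of the two endpoints.** A child above 1,000 copies/mL is also not suppressed, so the second event is nested in the first. Let q1 be the proportion not suppressed and q2 the proportion above 1,000. The correlation is

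r = √[ q2(1 − q1) / ( q1(1 − q2) ) ].

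The protocol gives control ranges of 65-85% suppressed (q1 15-35%) and 10-30% above 1,000, but no joint distribution. Every pairing below is therefore an assumption.

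**Step 3: chance of at least one false positive.** With no effect on either endpoint, and each test holding its 5%, this is P(|Z1| > 1.96 or |Z2| > 1.96) for a bivariate normal pair with correlation r.

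| Suppressed | Above 1,000 | r | At least one false positive |
| --- | --- | --- | --- |
| 80% | 20% | 1.00 | 5.0% |
| 75% | 20% | 0.87 | 7.3% |
| 80% | 15% | 0.84 | 7.5% |
| 70% | 20% | 0.76 | 8.0% |
| 75% | 15% | 0.73 | 8.2% |
| 70% | 15% | 0.64 | 8.6% |
| 65% | 10% | 0.45 | 9.2% |

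Worked example, 80% and 15%: r = √[0.15 × 0.80 / (0.20 × 0.85)] = √0.706 = 0.84.

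On a five-point grid over the protocol's control ranges, with fewer children above 1,000 than not suppressed, the result runs from 7.1% to 9.2%. It falls towards 5% as the two proportions converge. The ceiling, under independence, is 1 − 0.95² = 9.75%. A simulation with 199 children per arm agrees: 7.7% at 80%/15%, 8.2% at 75%/15% and 8.1% at 70%/20%.

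**Step 4: possible remedies.** A fixed sequence holds the overall error at 5% or less and leaves n at 199 evaluable per arm. Splitting alpha equally (0.025 each) would need 242 per arm for 80% vs 90%. 242 / 0.9 rounds up to 269, or 538 in total. At 199 per arm, power at 0.025 would be 71.1%.

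**The case against.** The strongest reply is that a testing order is often left to a separate analysis plan, which is not at hand, and that 5% per test is compatible with a fixed sequence or a both-must-succeed rule. The protocol also never says that success on either endpoint is enough. Its text leans towards suppression: the Summary ties roll-out to increased viral suppression, Expected Results calls suppression the primary endpoint, and Definition of Terms treats RNA >1,000 as a separate assessment. This stands in part. The inflation is conditional on how success is read, and a both-must-succeed rule would remove it. But the protocol contains its own Statistical Analysis Plan section, which sets 5% for one primary endpoint and carries the same approach to the other. An emphasis in the text is not a testing order.

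Two stronger readings are tempting, and the documents support neither.

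- A reader might take a narrow range such as 7.5-8.6% as this trial's error rate. It depends on chosen pairs of rates. The control rates of 80% suppressed and 20% above 1,000, which head the protocol's two power statements, taken together make the tests coincide, with no inflation. The protocol also gives 15% above 1,000 as an alternative, so inflation is possible but its size is not fixed.
- A reader might count retention as a third primary endpoint and add a further 5% test. No section lists three. The Summary names suppression and retention, and the objectives and sample-size sections name suppression and RNA >1,000. A three-test error rate would also need an assumption about how retention relates to suppression, and the protocol gives no figure for that.

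**Conclusion.** The point holds in a conditional form. Two primary endpoints each use the full 5%, with no stated order, split or joint rule. If either alone may support the claim that FAM-CARE works, the chance of at least one false primary claim is above 5%: about 7-9% over most of the protocol's planning ranges and never above 9.75%. It is 5.0% if no child has a detectable load at or below 1,000. These figures rest on assumed joint rates and on each test holding its own 5%. The protocol itself doubts the latter for the chi-square test, so they show the effect of having two tests and are not an estimate of the trial's actual error rate. Retention in the Summary is an inconsistency to reconcile, not a third primary test. The point deserves correction but does not undermine the design.

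**What to change.** State in the analysis section that the primary endpoints are tested in a fixed sequence at two-sided 5%. Suppression at 18 months comes first, and HIV RNA >1,000 copies/mL is confirmatory only if suppression is significant. This follows the emphasis already in the Summary and Expected Results. The sequence should be applied to one named analysis per endpoint.

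Reconcile the primary objective in the Summary with the objectives section, so that RNA >1,000 appears there and retention is described as secondary. Align the single-endpoint wording in Expected Results.

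The cost is wording only: the target stays at 444 and suppression loses no power. The downside is that if suppression is not significant, the RNA >1,000 result is descriptive, however strong it looks.

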**Secondary objectives:**

1. To evaluate the effect of a FAM-CARE program of HIV care on the proportion of children with viral suppression (undetectable HIV RNA levels) and with HIV RNA >1,000 copies/mL at 6 and 12 months after enrollment into the study.

*Hypothesis: Children in the FAM-CARE program will have improved viral suppression (undetectable RNA) and lower rates of HIV RNA >1000 copies/mL at 6 and 12 months compared to children in control facilities.*

1. Determine the individual and family factors associated with viral suppression and HIV RNA >1,000 copies/mLin children 18 months after enrollment in FAM-CARE and control facilities.
2. To evaluate the effect of a FAM-CARE program of HIV care on loss to follow-up (not seen in clinical care >3 months) and ART initiation in HIV-positive children not on ART at study entry.

*Hypothesis: Children in the FAM-CARE program will have lower rates of loss to follow-up and more children initiated on ART compared to children in control facilities.*

1. Evaluate the acceptability of the FAM-CARE program to caregivers and health care providers.

*Hypothesis: The FAM-CARE program will be acceptable to caregivers and health care providers.*

1. **EXPECTED RESULTS**

The FAM-CARE approach is a way of caring for children and their families within health services which ensures that care is planned around the whole family, not just an individual, and in which all family members are recognized as care recipients. The approach recognizes the vital role that families play in ensuring the health and well-being of infants, children, adolescents, and family members of all ages. It is hypothesized that such a family-centered care program will be successful in enrolling HIV-positive children, their HIV-positive mothers and their partners into continuous follow-up through incentivizing care-seeking within a family and reducing barriers to treatment and retention. Through clinic visits involving all HIV-positive family members, health care provider workload is decreased, as they will not have to see individual members of the family on different days; this also benefits the family by decreasing the amount of times they are required to come to the facility for clinic visits or to pick up ART.

Our study will:

- Assess the effect of the FAM-CARE program on rates of viral suppression and HIV RNA level >1,000 copies/mL in HIV-positive children on ART, and factors associated with these endpoints.

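### Secondary objective 2 estimates factor associations separately by arm, which splits the few unsuppressed children and gives no valid basis for saying that an association differs between arms

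*Protocol*

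**What the plan says.** Secondary objective 2 (Protocol, Secondary objectives) is to "Determine the individual and family factors associated with viral suppression", and likewise with HIV RNA >1,000 copies/mL, at 18 months in both kinds of facility. Unlike the other secondary objectives, it carries no hypothesis.

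The method is in the Protocol's Statistical Analysis Plan, under Data Collection and Management: "multilevel logistic regression models to estimate the association between viral suppression and putative factors in each study arm". The candidate factors are illustrative: "Examples of factors that might be evaluated include age and gender of child, when ART initiated and ART regimen, serious illness or hospitalization", followed by "timeliness of pharmacy drug pick-up, school attendance, family size, number of other HIV-positive individuals in family" and "HIV treatment and clinical status of other HIV-positive family members, disclosure of HIV status within family".

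The text for this objective mentions no model combining the arms, no arm-by-factor interaction and no other comparison of associations between arms. It states no significance level and no rule for selecting factors. The 5% level appears in the sample size section and in the primary comparison of two proportions.

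**The concern.** The information in a logistic model comes mainly from the rarer outcome, here children who are not suppressed. Estimating within each arm divides a small number of them in two, and unequally: if the programme works as hypothesised, FAM-CARE has about half as many as control. The same association is then harder to detect in FAM-CARE.

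Two things are at stake. First, real factors are more likely to be missed than they need be. Second, results laid out arm by arm invite comparison, and a factor that reaches significance in control but not in FAM-CARE is easily read as the programme having removed a barrier. That pattern can arise from fewer events alone. Separate estimates with no interaction give no valid test of whether the association differs.

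**Working it through.** **Inputs from the Protocol.** Table 3, row for 80% vs 90% suppression: 199 per arm, 398 in total, 444 after 10% loss. Study sampling procedures: about 666 children enrolled, 15% not on ART, and data from all enrolled children analysed.

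**Reproducing the plan's figure.** With pooled variance, two-sided 5% and 80% power:

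n = [1.96·√(2·0.85·0.15) + 0.842·√(0.8·0.2 + 0.9·0.1)]² / 0.10² = (0.990 + 0.421)² / 0.01 ≈ 199 per arm.

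199/0.9 = 221.1, rounded up to 222 per arm, or 444 in total. This agrees with Table 3.

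**Unsuppressed children per arm.**
- Unique-family count: 199 × 0.20 ≈ 40 control; 199 × 0.10 ≈ 20 FAM-CARE.
- All children on ART: 666 × 0.85 ≈ 566; 566/2 × 0.9 ≈ 255 per arm. This gives about 51 control and 25 FAM-CARE.
- For RNA >1,000, the 20% vs 10% case in Table 4 gives the same 40 and 20. The 15% vs 5% case gives about 30 and 10 with 199 per arm.

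**Assumptions (not in the Protocol).** A binary factor with prevalence 30-50%; the same odds ratio (OR) for non-suppression in both arms; independent outcomes; a two-sided 5% Wald test, used only as a yardstick.

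**Formulas.** Within an arm, SE² = 1/[n₁p₁(1−p₁)] + 1/[n₀p₀(1−p₀)], where n₁ and n₀ are the children with and without the factor. The risks p₁ and p₀ satisfy the OR and average to the arm's non-suppression rate. Power ≈ Φ(ln OR/SE − 1.96). The pooled SE is 1/√(1/SE_c² + 1/SE_f²), with c for control and f for FAM-CARE.

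**Worked case: OR 2, prevalence 50%, n₁ = n₀ = 99.5.**
- Control: p₀ = 0.146, p₁ = 0.254, SE = 0.366. Power = Φ(0.693/0.366 − 1.96) = 0.47.
- FAM-CARE: p₀ = 0.070, p₁ = 0.130, SE = 0.494. Power = 0.29.
- Pooled: SE = 0.294. Power = Φ(0.693/0.294 − 1.96) ≈ 0.65.
- Exactly one arm significant: 0.474 × 0.710 + 0.290 × 0.526 = 0.337 + 0.153 ≈ 0.49, of which 0.34 is control only.

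At 30% prevalence the powers are 0.47, 0.30 and 0.66 (pooled), and exactly one arm is again 0.49.

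**Range at 199 per arm, 80% vs 90%.**

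| OR in both arms | Exactly one arm significant |
|---|---|
| 1.5 | 0.27-0.28 |
| 2 | 0.49 |
| 2.5 | 0.51-0.52 |
| 3 | 0.41-0.47 |

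**Sensitivity at OR 2.**
- 255 per arm: power 0.57 and 0.36-0.37 by arm, 0.76-0.77 pooled.
- Lower control rates in Table 3 (75% vs 90%, 70% vs 85%, 65% vs 80%) at 199 per arm: the same formulas give control power from 0.52 to 0.63, FAM-CARE power from 0.29 to 0.47, and pooled power from 0.70 to 0.84. Exactly one arm stays near one half.

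**Power of an interaction.** With SEs 0.37 and 0.48, the SE of the difference in log odds ratios is √(0.37² + 0.48²) = 0.61. For a ratio of odds ratios of 2, power = Φ(0.693/0.61 − 1.96) ≈ 0.2.

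**The case against.** The strongest reply is that arm-specific estimates answer the objective as worded, which covers both kinds of facility. FAM-CARE acts on family-level factors, so associations may well differ by arm, and a pooled model without interactions assumes that they do not. The Protocol nowhere proposes comparing lists of significant factors between arms, so the misreading is a risk of the layout and not a planned analysis. The wording also does not strictly exclude arm-specific estimates taken from one model with interactions. Further, 199 per arm is a low denominator, and the 20 FAM-CARE events presume the full hypothesised benefit.

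Much of this stands. The common-association assumption is a genuine cost of pooling, and interaction power is low. But the separate analysis has no better power to detect a difference between arms; it only leaves that question untested. The advantage of pooling persists at 255 per arm and at lower control suppression rates.

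A reader might also infer a heavy multiplicity problem: 11 listed factors × 2 arms × 2 outcomes = 44 tests at 5%, screened by significance. The document does not support this. The factors are examples, the model clause names only suppression (11 × 2 = 22 if taken literally), and no significance level or selection step is set for this objective. Multiplicity handling, an exploratory label and the final factor list may properly sit in the statistical analysis plan.

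**Conclusion.** The point holds as a cheap improvement to a secondary objective. The stated method divides about 60 unsuppressed children (about 76 on the larger denominator) between two separate analyses and provides no test of whether associations differ. At an odds ratio of 2 in both arms, power is 0.47 and 0.29-0.30 by arm against about 0.65 pooled. About half the time the factor would be significant in one arm only.

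These figures rest on the design rates, the assumed factor prevalence and odds ratios, a 5% yardstick that the Protocol does not set for this objective, and independence. Correlation within families or facilities would change them.

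It would go too far to say that the models are overfitted. The Protocol does not say that all factors enter one model, so events per factor cannot be computed from it. Neither primary endpoint is affected.

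**What to change.** In the Protocol's Statistical Analysis Plan, replace the instruction to model within each arm with the following:
- one multilevel logistic model for each outcome (suppression, and RNA >1,000 copies/mL), pooling both arms and including study arm as a term;
- any statement that a factor acts differently by arm to rest on an arm-by-factor interaction, for a short list named in advance;
- arm-specific estimates with 95% intervals shown descriptively.

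This changes analysis wording only and needs no further data. The cost is that factors without an interaction term are assumed to have a common association in both arms. Interaction tests will also have low power, about 0.2 for a ratio of odds ratios of 2, so a non-significant interaction should not be reported as evidence that the association is the same.
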